## Abstract

Intimate partner violence (IPV) is a public health problem that psychologically and physically affects the women who suffer from it. In this article, we propose an intervention protocol based on therapeutic tourism through adventure physical activities and psychological therapy that could improve the psychological and physical health of women participants. We propose a randomized study where participants will be separated into two groups, control and experimental, and we will perform measurements including self-concept, self-image, depression, and perceived stress, combining these with physiological measurements of stress level by determining stress-related hormones (Cortisol and DHEA), as well as the overall cost-effectiveness of the program. All data collected at the end of the protocol will be statistically analysed. If the final data are positive and it is feasible, this protocol could be proposed as a measure for the treatment of the sequelae of victims of gender violence.

## 1. Introduction

Currently, there is a growing concern about health and well-being-related topics, triggered by the global pandemic we experienced since March 2020. Therefore, the 2030 Agenda developed by the United Nations (UN) has included health and well-being among the Sustainable Development Goals (SDGs) [1]. Hence, within SDG-3, Health and Well-being, mental health promotion has a privileged place, due to the alarming increase in mental health problems, and warning the World Health Organisation (WHO) that by 2030 these disorders will be the leading cause of disability in the world [2].

Therapeutic tourism brings together both the WHO definition of health tourism and the World Tourism Organisation (UNWTO) definition as an activity that involves a person travelling to a place other than their place of residence to receive a health intervention through tourist services, products, or experiences that the destination promotes and offers González, et al. [3]. There are several approaches within this therapeutic tourism including, on the one hand, the medical-clinical, focused on pathology, aesthetic or reproductive issues, and on the other hand, wellness tourism, which impacts overall health González, González and Hernández [3]. This project will focus on the second one, as the tourism motivation will (1) improve or maintain physical health and appearance, (2) improve or maintain mental health, (3) restore self-esteem, (4) the importance of others, (5) self-discovery, (6) personal development, (7) transformation of oneself and (8) specialisation of the destination in a specific therapy or service [3,4]. The Jerte Valley is one of the most well-known and consolidated tourist destinations in Extremadura, positioned nationally as one of the most popular destinations in rural and nature tourism. Due to its orography, it offers optimal conditions for the practice of various physical activities in nature and adventure sports, hosting more than 70% of the Active Tourism companies in Extremadura [5]. Consequently, the Jerte Valley natural environment has the proper attributes to become a successful therapeutic tourism destination, given as its characteristics include tourist-resident interaction in the tourist destination, natural landscape, suitable climate and landscape as a whole, pollution-free location, the existence of a suitable therapeutic tourism offer, safety in general and health safety in particular [3,6,7,8,9].

The UN defines violence against women (VAW) as any act of gender-based violence that results in or is likely of resulting in, physical, sexual, or mental harm or suffering to women, including threats of such acts, coercion, or arbitrary deprivation of liberty, whether occurring in public or private life and may include different forms of violence such as intimate partner violence (IPV), sexual violence, human trafficking, female genital mutilation, or child marriage [10,11,12]. IPV is committed by a current or former intimate partner and is considered the most common form of violence experienced by women, resulting in physical, psychological, and sexual violence or stalking; one in three women in a relationship has experienced IPV, according to the UN [13]. Gender violence has serious consequences for women’s health, particularly post-traumatic stress disorder (PTSD) as a consequence of the suffered violence [14,15]. Women, as a consequence of IPV, have a damaged body image which leads to a negative self-concept [16] and aggravates the PTSD symptomatology [17]. Moreover, PTSD impacts people’s well-being; in the case of IPV victims, affecting their well-being and physiological responses [18,19]. Several studies have analysed the endocrine and immune consequences of IPV, revealing disturbances in the pituitary-adrenal axis functioning of the hypothalamus [20]. It has also been found that IPV victims who developed PTSD have elevated levels of cortisol during the day, with is associated with this hormone production dysregulation leading to physical stress symptoms and other associated pathologies [21]. IPV victims also have higher nocturnal cortisol levels of dehydroepiandrosterone (DHEA) compared to women who have not been IPV victims [13].

The connection with nature can be an alternative approach for people with psychological problems [22]. Nature therapy combines several techniques that address factors in the origin and maintenance of psychosocial problems, making it more effective than individual techniques. Studies have demonstrated its many beneficial features, such as its focus on direct user participation and responsibility, its interaction with the natural environment, and its attention to problem-solving [23]. Moreover, the American Psychological Association (APA) recommends its use for IPV victims [24]. To date, a protocol for a multicomponent cognitive-behavioural program based on therapeutic tourism has been published [25]. However, no measurements of physiological aspects were carried out in this study. Then, as therapeutic tourism has suitable properties to work with IPV victims [26] and to advance knowledge in this field, this study will aim to analyse the effects of a multicomponent program combining psychological therapy and adventure sportive activities in the Jerte Valley to improve the general well-being and health of IPV victims, assessing biological markers of stress and aspects related to mental health.

## 2. Materials and Methods

### 2.1. Study Design and Ethical Considerations

A parallel-group randomized controlled trial will be conducted including a one-month intervention phase. Both for the control group (CG) and experimental group (EG), evaluations will be carried out before the start of the intervention (initial assessment), as well as at the end of the intervention (final assessment). The study will be carried out according to the Consolidated Standards of Reporting Trials Statement (CONSORT) methodology for randomized controlled trials [27].

The Ethics Committee of the University of Extremadura University approved this project (approval code: 45/2022), which will follow the Declaration of Helsinki and their actualizations as amended by the 64th General Assembly of the World Medical Association (Fortaleza, Brazil, 2013) and the Biomedical Research Act 14/2007. Moreover, this study has been registered with the International Standard Randomised Controlled Trial Number (registration number: ISRCTN93835057; https://www.isrctn.com/) (accessed 26 October 2022).

### 2.2. Sample Size

Assuming a dropout rate, and accepting an alpha risk of 0.05 and a beta risk of 0.2 in a two-sided test, 11 subjects should be necessary for the intervention and 11 in the control group to recognize, as statistically significant, a difference greater than or equal to 0.18 units [28]. The common standard deviation was assumed to be 0.15 [29], and the correlation coefficient between the initial and final measurement, was 0.6 [30].

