### 2.6. Measures and Instruments

Various instruments will be used to assess the feasibility and effectiveness of the multi-component program. Evaluation will be carried out in both EG and CG at baseline and post-intervention.

Self-reported psychological assessment will include the following instruments in a paper format booklet:-Brief socio-demographic data sheet: this will include questions related to age, gender, educational level and socio-economic status, etc., and gender-based violence history (questions to assess lived experiences of gender-based violence).-Baessler and Schwarzer’s General Self-Efficacy Scale [32]. It aims to assess a stable sense of personal competence to deal effectively with multiple stressful situations. This questionnaire is composed of 10 items with a 4-point Likert-type response.-Rosenberg Self-Esteem Scale [33]. The scale assesses feelings of self-respect and self-acceptance. The scale includes ten items, half of which are stated positively and half negatively. The items are answered on a 4-point Likert scale (1 = strongly agree, 2 = agree, 3 = disagree, 4 = strongly disagree), and the total score ranges from 10 to 40. Participants will complete the Spanish version adapted by Morejón, et al. [34] (α= 0.72 to 0.88).-Body Shape Questionnaire (BSQ) [35]. This questionnaire assesses the presence of concern and dissatisfaction with body image. It measures dissatisfaction with one’s own body, fear of gaining weight, low self-concept about physical appearance, and desire to lose weight. It consists of 34 items including 4 subscales (body dissatisfaction, fear of gaining weight, low esteem related to appearance, and desire to lose weight) which are measured on a 6-point scale, ranging from “never” to “always”. The total score ranges from 34 to 204, with higher scores showing greater body dissatisfaction. The Spanish validation of Raich, et al. [36], will be completed by participants (α = 0.95 to 0.97) [36].-Beck Depression Inventory, Second Edition (BDI-II) [37]. This is a questionnaire that assesses the presence and severity of depression in adolescents and adults. This consists of 21 items from different areas such as sadness, loss of pleasure, suicidal ideation, etc. Scores range from 0 to 63, including different cut-off points to classify patients according to the following subgroups: normal to minimal depression (0 to 13), mild depression (20 to 28), moderate depression (20 to 28), and severe depression (scores above 29) (α = 0.83) [38].-Perceived Stress Test (PSS) [39]. The PSS assesses the perception of control over environmental demands. It is a self-report instrument consisting of 14 items with a five-point scale response format (0 = never, 1 = hardly ever, 2 = occasionally, 3 = often, 4 = very often). A higher total score obtained is an indication of a higher level of perceived stress (α = 0.82 to 0.81) [40].-EQ-5D-5L. The EQ-5D-5L [41] is a questionnaire that aims to assess health-related quality of life (HRQoL). It is composed of 5 dimensions (mobility, self-care, usual activities, pain or discomfort, and anxiety or depression), with five possible response levels. Health states can be described by a 5-digit number, where the first number is the response to the first question, the second number is the response to the second question, and the third number is the response to the third question. is the answer to the first question, the second number is the answer to the second question, and so on. Given Since the EQ-5D is a preference-based questionnaire, these health states can be converted into a utility index by applying the appropriate formula. This instrument also includes a Visual Analogue Scale (VAS) with a range from 0 (worst imaginable health state) to 100 (best imaginable health state). (best imaginable health state).-Physiological measures will include glucocorticoids, cortisol, and dehydroepiandrosterone (DHEA) analysis through saliva samples. The participants will provide a minimum of 0.5 mL of saliva in a plastic tube recipient Salitubes SLV-4157 (DRG Instruments GmbH, Marburg, Germany) specifically to be used with DRG Salivary Cortisol/DHEA ELISA Kits (DRG Instruments GmbH, Marburg, Germany) twice a day (between 8 and 9 AM for DHEA and cortisol, and between 8 and 9 PM for evening cortisol). All samples will be triplicated to ensure process reliability. Participants will be instructed to collect samples in their homes. Saliva samples will be frozen in women’s freezers and will be brought to the Department of Anatomy of the University of Extremadura medicine Faculty in a mobile freezer, where they were being kept frozen at 21 °C previously to be analysed following the protocol indicated in the kits.

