### 2.8. Statistical Analysis

All data and analyses will be collected and analysed with the SPSS statistical package (version 26.0; SPSS, Inc., Chicago, IL, USA). The Shapiro-Wilk test will be performed to check data normality and to choose between parametric or non-parametric statistical analyses. Continuous socio-demographic variables will be presented as mean (SD) or median (IR) where appropriate, while categorical variables will be presented as proportions. Differences between groups at baseline will be analysed using independent samples t-tests. To assess the effects of the program, two types of analyses will be conducted. Intervention effects will be assessed using a repeated measures ANCOVA test, adjusted for age and baseline values. Cohen’s d (with a 95% confidence interval) will be also included in the results as the effect size. Effect size thresholds will be interpreted as follow: >0.2, small; >0.5, moderate; >0.8, large [46]. Statistical significance will be computed for the effect of time and the interaction group × time. The alpha level will be fixed at *p* ≤ 0.05.

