## 4. Conclusions

If positive results on women’s emotional well-being are obtained, and if it is a cost-effective type of intervention, the implementation of multi-component programmes using the resources of therapeutic tourism could be a tool to empower and support the mental health of these women, as well as optimising costs for the social and health systems.

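### The stated 80% power and 5% alpha belong to an unnamed outcome; no primary outcome is designated, and about ten outcomes are tested at 0.05 with no order among them

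*Protocol article*

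**What the plan says.** Section 2.2 sets the sample size by "accepting an alpha risk of 0.05 and a beta risk of 0.2 in a two-sided test", giving 11 women for the intervention and "11 in the control group to recognize, as statistically significant, a difference greater than or equal to 0.18 units". It adds that "The common standard deviation was assumed to be 0.15" and that the correlation between initial and final measurement is 0.6. The three values carry citations, but no instrument, scale or unit is given.

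Section 2.6 opens with "Various instruments will be used to assess the feasibility and effectiveness of the multi-component program" and lists the instruments without ranking them. Section 2.8 states "The alpha level will be fixed at" p ≤ 0.05 and "Statistical significance will be computed for the effect of time and the interaction group × time". It describes no hierarchy among outcomes and no adjustment.

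Section 4 makes its recommendation depend on positive results for the women's emotional well-being, which "are obtained, and if it is a cost-effective type of intervention" then qualifies. It does not say which scale, or how many, must show an effect.

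**The concern.** Alpha and power are properties of one test on one outcome. A sample-size statement that omits the outcome cannot be interpreted, and a reader will tend to attach the 80% to whatever the conclusion is about. Here that is emotional well-being, and the figures do not look as if they came from the scales that measure it.

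About ten outcomes then share one significance threshold, and nothing marks one of them as decisive. As written, a claim of effect could be built on whichever scale reaches 0.05, without the error control or the power stated in Section 2.2. The tests of the time effect add a second p-value per outcome, and that p-value does not compare the groups.

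**Working it through.** **1. The plan's own figure.** Inputs from Section 2.2: difference 0.18, SD 0.15, two-sided alpha 0.05, power 0.80. For two independent means, n per arm = 2 × [SD × (1.960 + 0.842) / difference]² = 2 × [0.15 × 2.802 / 0.18]² = 10.90, so 11. The stated number reproduces (normal approximation, ignoring the correlation and dropout). With change scores at correlation 0.6, the SD is 0.15 × √(2 × 0.4) = 0.134 and n = 8.72; dividing by 0.80 for an assumed 20% dropout gives 10.9, again 11. The article does not state the dropout rate, so it cannot be seen which route was used. Either way the number follows from the inputs, and the standardised difference is 0.18 / 0.15 = 1.2 SD.

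**2. Do 0.18 and 0.15 fit the scales?** Section 2.6 describes total scores of 10–40 (Rosenberg), 34–204 (BSQ) and 0–63 (BDI-II), and 14 items scored 0–4 (PSS). These totals are whole numbers. An SD of 0.15 is a variance of 0.0225. If scores took only two adjacent values, p(1 − p) = 0.0225 gives p = 0.023, so about 98% of women would have the same score. That is implausible for any of these totals. The values could fit a quantity on a smaller numerical scale, but the article does not say which.

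**3. Outcomes counted from Section 2.6.** Self-efficacy, self-esteem, BSQ total, BDI-II, PSS, EQ-5D-5L index, VAS, morning cortisol, evening cortisol and DHEA make ten. The first five are the psychological scales.

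**4. Chance of at least one false significant group difference.** Assumptions: no true effect on any outcome, one group test per outcome at two-sided 0.05, and any single significant result taken as success. If independent:

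- ten outcomes, either direction: 1 − 0.95¹⁰ = 0.401
- ten outcomes, benefit only: 1 − 0.975¹⁰ = 0.224
- five scales, either direction: 1 − 0.95⁵ = 0.226
- five scales, benefit only: 1 − 0.975⁵ = 0.119

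With equal pairwise correlation, by simulation (400,000 draws of normal statistics, cut at 1.96):

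| Assumed correlation | Ten, either direction | Ten, benefit only | Five, either direction | Five, benefit only |
|---|---|---|---|---|
| 0 | 40% | 22% | 23% | 12% |
| 0.3 | 35% | 18% | 21% | 10–11% |
| 0.5 | 29% | 14% | 18% | 9% |
| 0.7 | 21% | 11% | 15% | 7% |

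Simulated t-tests with 11 per arm give nearly the same for ten outcomes: 40%, 35%, 29% and 22% in either direction. The benchmark for one two-sided test is 5% in either direction and 2.5% for benefit. The time-effect tests are left out of all these figures.

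**5. What 11 per arm can detect on another scale.** Turning the formula in step 1 round, the detectable difference is 2.802 × √(2/11) = 1.19, or about 1.2 SD. Section 2.8 calls 0.5 SD moderate. At 0.5 SD, 11 per arm gives about 20% power by t-test, or about 29% with baseline adjustment at correlation 0.6 (residual SD factor √(1 − 0.36) = 0.8).

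**The case against.** The strongest reply is that this is a condensed article of a registered trial. Multiplicity methods are commonly left to an analysis plan, and the cited sources or the registry record may identify the outcome. That stands for the choice of adjustment, which is not faulted here. It does not cover Section 2.2, which states a power claim that cannot be read without its outcome, or Section 2.8, which itself fixes the threshold.

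Several stronger readings are tempting, and the document does not support them:

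- A reader might infer a 30–40% chance of a false positive result. That counts significant worsening as success and takes all ten outcomes, whereas Section 4 speaks of benefit on emotional well-being. It also needs low to moderate correlations, which the article does not give, and a one-is-enough rule, which it does not state. Section 4 adds cost-effectiveness as a further condition.
- A reader might call an SD of 0.15 impossible on any questionnaire. No scoring range is given for the self-efficacy scale, and scoring by item means is not excluded. Implausible for the totals described is as far as the text goes.
- A reader might add the four BSQ subscales and count 14 tests. The subscales are described, but nothing says that they will be tested.
- A reader might conclude that the sample size is wrong. It reproduces from its inputs.

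**Conclusion.** The point holds in this form: the alpha and power statement is tied to no named outcome, no primary outcome is designated, and about ten outcomes share one threshold with no order among them. The conclusion in Section 4 concerns scales to which the 0.18 and 0.15 probably do not belong, so neither the 80% power nor the 5% error rate can be taken to cover it.

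The size depends on assumptions. If one significant outcome were enough, a false benefit would arise in about 14–22% of such trials over ten outcomes, or 9–12% over the five psychological scales, for assumed correlations from 0.5 down to 0. That is roughly four to nine times the 2.5% of a single two-sided test. Higher correlations would lower these rates. A false difference in either direction over ten outcomes is 29–40% on the same assumptions.

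This should be corrected before any unblinded analysis, because a primary outcome chosen after the results are seen cannot restore the error guarantee.

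**What to change.** In Sections 2.2 and 2.8, before unblinded analysis:

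- Name the outcome and unit from which 0.18 and 0.15 were taken, and make it the single primary outcome.
- Make its between-group difference (group × time, or baseline-adjusted) the primary test at two-sided 0.05, and state that the 80% power applies to that outcome only.
- Label all other outcomes, and all time effects, as secondary or exploratory. Report them as estimates with 95% confidence intervals and not as grounds for a success claim. A formal adjustment such as Holm is an option, not a requirement.
- Reword Section 4 so that a positive result means the primary outcome.

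If an emotional well-being scale is meant to be primary, name it and restate in its own points the difference that 11 per arm can detect, about 1.2 SD on the plan's plain two-means inputs. The article gives no SD for these scales, so one would have to be justified, and whether 11 per arm is then enough is open.

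Otherwise the cost is wording, plus the registry entry if it differs, and no additional women. The downside is that fewer outcomes can support a claim of effect.

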### 2.3. Randomisation and Blinding

Participants will be randomized 1:1 to the intervention (usual care + multi-component plan) or the control group (usual care). A research team member who will not be directly involved in the trial will create a simple computer-generated randomization sequence using the software Research Randomizer (version 4.0; http://www.randomizer.org, accessed on 20 April 2022) [31]. The assignment will be hidden with a password-protected file. The researchers involved in the data analysis processes will not be aware of the group to which each woman will be assigned (EG or CG).

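### Simple randomisation does not secure the planned 11 women per arm; a restricted sequence would, at almost no cost (minor, cheap improvement)

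*Protocol article*

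**What the plan says.** Section 2.2 (Sample Size) of the protocol article concludes that "11 subjects should be necessary for the intervention and 11 in the control group". It bases this on "accepting an alpha risk of 0.05 and a beta risk of 0.2 in a two-sided test", "a difference greater than or equal to 0.18 units", "The common standard deviation was assumed to be 0.15" and a statement that "the correlation coefficient between the initial and final measurement, was 0.6". It opens with "Assuming a dropout rate" but gives no rate.

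Section 2.3 (Randomisation and Blinding) says "Participants will be randomized 1:1 to the intervention" or to control, and that a team member outside the trial "will create a simple computer-generated randomization sequence using the software Research Randomizer". The list is concealed in a password-protected file. The section mentions no blocks, strata or fixed number per arm.

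Section 2.5 (Intervention) gives the experimental arm its psychological component as group therapy, followed by adventure activities on weekend outings. It states neither a group size nor the number of groups.

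**The concern.** In trial usage, simple randomisation means that each woman is allocated independently, like a coin toss. The 1:1 ratio then holds in expectation, but the realised arm sizes are random. In a trial of several hundred this hardly matters. With 22 women, noticeable departures from equality are common, and precision is lost whenever the arms differ in size. The trial runs on a single sequence, so an average over all sequences does not protect it from a poor one, and the split cannot be corrected after allocation.

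A second consequence is possible because the programme is delivered in a group: the allocation would also set how many women attend the therapy session and the outing.

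**Working it through.** **Inputs.** From Section 2.2: difference 0.18, SD 0.15, correlation 0.6, two-sided alpha 0.05, power 80%, 11 per arm. From Section 2.3: simple 1:1 allocation. The dropout rate is not given, so 0% (22 analysed) and an assumed 20% (22 × 0.80 = 17.6, about 18 analysed) are both shown.

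**Reproducing the 11 per arm.**
- SD of the change score: 0.15 × √(2 × (1 − 0.6)) = 0.134.
- n per arm = 2 × (0.134 × (1.960 + 0.842) / 0.18)² = 8.72, so 9.
- With 15% dropout, 9 / 0.85 = 10.6, so 11. With 20%, 8.72 / 0.80 = 10.9, so 11.
- The match is not unique: the unadjusted SD of 0.15 without dropout gives 10.9, also 11.

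**Arm sizes under simple randomisation.** The number in the experimental arm is Binomial(22, 0.5), and 2²² = 4,194,304.
- Exactly 11:11: C(22,11) / 2²² = 705,432 / 4,194,304 = 16.8%.
- A smaller arm of k or fewer (k < 11) has probability 2 × Σ C(22,j) / 2², summed over j = 0 to k, with the denominator again 2²² = 4,194,304. For k = 8 this is 2 × 600,370 / 4,194,304 = 28.6%.

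**Variance.** Relative to 11:11, the variance of the group difference is (1/k + 1/(22 − k)) / (2/11) = 121 / (k(22 − k)).

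**Power, all 22 analysed.** Normal approximation on the change score: Φ(0.18 / (0.134 × √(1/k + 1/(22 − k))) − 1.960).

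| Split | Probability of this split or worse | Rise in variance | Power at this split |
|---|---|---|---|
| 11:11 | – | 0% | 88.2% |
| 10:12 | 83.2% | 0.8% | 88.0% |
| 9:13 | 52.3% | 3.4% | 87.2% |
| 8:14 | 28.6% | 8.0% | 85.7% |
| 7:15 | 13.4% | 15.2% | 83.4% |
| 6:16 | 5.2% | 26.0% | 80.0% |

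Weighting every split by its probability gives an average power of 86.6%, which is 1.7 points below the balanced 88.2%.

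**Check on the approximation.** With the t distribution in place of the normal, the change-score power is 84.9% balanced and 83.1% on average, a loss of 1.8 points. At single splits it is 82.1% at 8:14, 79.6% at 7:15 and 76.0% at 6:16. Simulation of an ANCOVA with baseline and age as covariates (12,000 runs each) gives 88.5% balanced and 86.6% on average with 22 analysed, and 78.7% and 76.6% with 18 analysed. On each method the average loss is about 2 points.

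**The case against.** The case for leaving the text alone is substantial.

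- **Simple randomisation is valid.** It is unbiased and the least predictable scheme. Section 2.3 describes masking only for the data analysts, so unpredictability has value here. This stands.
- **Most sequences cost little.** A 10:12 split is not a failure, since it adds only 0.8% to the variance. About 71% of sequences (100% − 28.6%) cost 3.4% or less. This stands, and it is why the 16.8% for exact balance should not be read as the size of the harm.
- **Section 2.2 and Section 2.3 can both be true.** The 11 per arm is a planning requirement, and 1:1 is an allocation ratio that simple randomisation honours in expectation. So this is not a strict contradiction; the stated method merely fails to secure the planned numbers.
- **The wording may be loose.** 'Simple' may only mean an uncomplicated computer list, perhaps with fixed totals. That is possible, but nothing in Section 2.3 says so and the term has a standard meaning. A method has been stated, so this is not a complaint about missing detail.
- **Chance imbalance in covariates is partly handled.** Section 2.8 adjusts for age and baseline values. That helps with those variables but does not restore equal arm sizes.

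A reader might infer that simple randomisation leaves the trial underpowered. The documents do not support this. With all 22 analysed, the normal approximation still gives 80.0% at 6:16; the t-based change-score figure falls below 80% only from 7:15 outward. With 18 analysed the balanced ANCOVA is already at 78.7%. That shortfall comes from an assumed dropout rate, and simple randomisation adds only about 2 points to it.

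A reader might also infer that a group of 7 or 15 women would alter the programme. Section 2.5 states no group size, limit or number of cohorts, so this is not shown.

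**Conclusion.** The point holds as a minor, cheap improvement. As worded, Section 2.3 does not secure the 11 + 11 of Section 2.2. A split of 8:14 or worse, with at least 8% more variance, would arise in 28.6% of sequences; 7:15 or worse, with at least 15% more, would arise in 13.4%. The expected loss of power is about 2 points, and there is no bias.

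The arm-size probabilities assume that 22 women are randomised and that 'simple' means unrestricted. The power figures rest on the article's own inputs, and those for 18 women rest on the assumed 20% dropout. The remark on group size assumes that the experimental arm is treated as one group.

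**What to change.** In Section 2.3, replace the simple sequence with a restricted one and name it:

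- If all women can be enrolled and assessed at baseline before allocation, use one random permutation of 11 experimental and 11 control labels, applied in a single batch. This fixes the arms at 11:11 and leaves no later allocation to predict.
- If enrolment is staggered, use permuted blocks of randomly varying size, with the block sizes concealed from those who recruit. The arms then stay close to equal.

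If a list with fixed totals was intended all along, it is enough to say so.

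The cost is close to nil: the same uninvolved team member prepares the list and the same password protection applies. The one drawback is that blocking makes late allocations slightly more predictable. Varying block sizes and concealment limit this, and single-batch allocation avoids it. The change has to be made before randomisation.
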